Best practices for decision aids require a values clarification (e.g., helping patients to think about which aspects matter most to them) and explanation that a patient is free to choose nontreatment. (Source: National Quality Forum. National Standards for the Certification of Patient Decision Aids. Final Report. December 15, 2016.) Therefore, we have created written materials (attached) to explain that their provider would like to discuss some things about which there is no “right” answer; introduce shared decision making; explain that both patients and providers play important roles; their doctor wants them to participate; and prompts to ask questions. Four possible versions are attached; we will try different versions and evaluate feedback until we find a preferred version. Based on provider and patient feedback that it is important not to overwhelm with too much information during the appointment, we may provide this information to patients with the mailed informational letter, shortly after check-in for their appointment, and/or shortly after they finish with their provider (before they leave). For patients who receive

| Table 1. Summary Statistics        |               |                    |            |
|-------------------------------------------|---------------|--------------------|------------|
| Patients aged 50-64 y seen in 2015 |               |                    |            |
|                                           |               | Main Campus | STJ |
| N patients                                |               | 7,550              | 2,567      |
| N wellness visits                         |               | 2,456              | 402        |
| Gender                                    | Female        | 58%                | 58%        |
| Race                                      | Black         | 47%                | 84%        |
| Smoker                                    | Current       | 17%                | 39%        |
| Obese (BMI $\geq 30.0$ )                  |               | 41%                | 47%        |
| BP                                        | $\geq 140/90$ | 9%                 | 13%        |
| LDL                                       | 100-159       | 40%                | 36%        |
|                                           | $\geq 160$    | 6%                 | 5%         |
| Diabetes Diagnosis                        |               | 29%                | 40%        |

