|                                           | HbA1c $> 9$   | 4%                 | 7%         |
| Overdue: colorectal cancer screening      |               | 37%                | 46%        |
| Zip code median income $< \$25,000$       |               | 31%                | 61%        |
| Medicaid                                  |               | 5%                 | 44%        |

the values clarification before their appointment, we may provide their written individualized recommendations at that time and/or during their appointment.

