Simultaneous to Aim 1, we will develop a web portal on which a user may input all model parameters and receive the tailored decision aid. Following methods from prior research, we then will conduct practice runs (to simulate workflow) and iterative rounds of pilot testing (likely 3 to 4) in short bursts of approx. 2-4 weeks. To minimize risk of attrition, we will include only a subset of the approx. 10 providers in each round, so that each provider only participates once. (Providers may choose to continue based on interest.) Each week, the study team will identify eligible patients who have appointments with participating providers approx. 2-4 weeks later (obtained by data feed from our EMR group; our institution routinely uses this process.) Study staff will contact eligible patients by mail, telephone or in waiting rooms (see attachment). Study staff then will review the chart, manually enter model inputs, and distribute a printed copy of the tailored decision aid to each patient's providers. Additional copies will be provided on the day of appointment. Providers will be the research subjects. Providers will be asked to show each patient his/her individualized recommendations and engage in shared decision making about preventive care goals. At the end of the visit, a medical assistant or study staff will hand the patient a printed copy of the decision aid to take home, along with an after-visit summary that s/he already provides ***Feedback:*** We will seek feedback from participating providers. Feedback may be in whatever form is most convenient for each provider (oral, written, email, etc.). Additionally, we will inform patients that their doctor is participating in a research study, and ask patients if they would be interested in providing feedback in the form of a 10-15 minute survey. The patient will **not** be required to complete the survey. If the patient chooses to complete the survey, then s/he will receive \$25. We do not require any pre-specified number of patients to agree. We chose this method as a variant of prior work that has cluster randomized clinical practices to early vs. delayed intervention (where controls were patients in the delayed group before implementation), recognizing the non-randomized, exploratory nature of our study. For providers, our goal from feedback will be to create a tool that is easily understood, that providers are interested in using, and that providers believe improves the patient visit and facilitates shared decision-making. For patients who choose to complete the survey, outcomes measures (Appendix C) will include: use of shared decision making (Shared Decision Making-Q-9—e.g., “My doctor told me there are different options for preventive care”, “My doctor and I selected preventive care options together”) and plans for preventive care activity over the next 1 month and 6 months.

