
## **Phase II pilot testing**

As Phase I pilot testing winds down, the research team will conduct a subsequent phase of pilot testing that is broader and includes randomization. The protocol for Phase II pilot testing is the same as for Phase I, with the following exceptions:

1. Instead of just physicians, pilot testing may be conducted with any primary care provider (e.g., physicians, physician assistants, nurse practitioners, registered nurses),
2. Pilot testing may be conducted at any Cleveland Clinic internal medicine, community internal medicine, or family medicine department. There is no targeted number of practice sites or providers.

- 707 3. Shortly before each appointment at which the decision aid may be discussed, the visit  
708 will be randomized to “intervention” or “control.” During intervention appointments,  
709 the individualized recommendations will be made available to providers as per Aim  
710 1. During control appointments, the research team may still generate individualized  
711 recommendations but will not make them available to providers. Regardless of  
712 whether the appointment was intervention or control, the patient will still be informed  
713 that their doctor is participating in a research study, and we will ask patients if they  
714 would be interested in providing feedback in the form of a 10-15 minute survey, as  
715 per Aim 1. As with Aim 1, the patient will **not** be required to complete the survey.  
716
- 717 4. Patients who choose to complete the survey will be notified that after their  
718 appointment, we may review their medical record to see which health care services  
719 they receive during the next 1 year. Providers will be similarly notified that we may  
720 review the medical records of their study patients. The purpose of this review is to  
721 see whether provider conversations had an impact on which preventive services were  
722 ultimately provided to patients. To ensure that patients are aware of this, we will only  
723 review the medical records of patients who chose to complete the survey. This  
724 process presents no more than minimal risk of harm to subjects and involves no  
725 procedures for which written consent is normally required outside the research  
726 context.  
727
- 728 5. We will use a different survey from Phase I pilot testing. While Phase I pilot testing  
729 is primarily intended for general feedback on the design of individualized preventive  

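### Amendment 4 withholds the individualised recommendations at control visits from providers only; the steps inherited from Phase I that hand them to patients carry no arm restriction.

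*Supplement*

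**What the plan says.** All references are to the Supplement, Amendment 4, the latest full protocol text.

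- **Inheritance.** Phase II pilot testing opens: "The protocol for Phase II pilot testing is the same as for Phase I, with the following exceptions". Six exceptions follow.
- **Randomisation.** Exception 3 sets the time: "Shortly before each appointment at which the decision aid may be discussed, the visit" is randomised. No interval is given.
- **Intervention visits.** Exception 3: "the individualized recommendations will be made available to providers as per Aim" 1.
- **Control visits.** Exception 3: the team may produce individualised "recommendations but will not make them available to providers".
- **Generic materials to patients.** Under Phase I pilot testing, written sheets on shared decision making and values clarification may go "to patients with the mailed informational letter, shortly after check-in for their appointment, and/or shortly after they finish" with the provider.
- **Individualised recommendations to patients before the visit.** Under Phase I pilot testing, for patients who receive "the values clarification before their appointment, we may provide their written individualized recommendations at that time and/or during their appointment".
- **Take-home copy.** Under Phase I pilot testing, clinic or study staff are to "hand the patient a printed copy of the decision aid to take home" when the visit ends.
- **Lead time.** Eligible patients are identified about 2 to 4 weeks ahead and contacted by post, by telephone or in the waiting room.
- **Outcomes.** The survey may be completed straight after the visit or within 3 business days. For patients who complete it, the medical record may be reviewed over the following year.

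**The concern.** The randomised comparison depends on control patients not receiving the individualised recommendations. Exception 3 protects the provider's side only, and everything it leaves untouched is inherited. Staff who followed the text to the letter could give a control patient the written recommendations before the visit, or the printed aid at its end.

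Either would weaken the contrast that Phase II was randomised to create. A copy received before the visit could change the conversation that SDM-Q-9 scores. A copy received at the end is less likely to affect the rating of a conversation already held, but it could change stated intentions for the next 1 and 6 months and the services used over the next year. Amendment 4 does not ask for a record of what each patient received, so any dilution could be neither measured nor adjusted for.

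Phase II may run in any internal medicine, community internal medicine or family medicine department, with no target number of sites. Two departments could both comply with the protocol and run different control conditions.

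**Working it through.** The point rests on the text, and Amendment 4 has no figure to reproduce.

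**Step 1: which exception defines control?** Only exception 3. Exceptions 1 and 2 widen the providers and sites, 4 concerns record review, 5 the survey, and 6 the eligibility of Phase I participants. None limits what a control patient may be given.

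**Step 2: what is inherited, and when does it happen?**

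| Inherited Phase I step | Content | Wording | Timing against randomisation | Limited by arm? |
|---|---|---|---|---|
| Shared-decision and values sheets | Generic | Optional | With the letter: possibly before. At check-in or after the visit: may be after | No |
| Written recommendations before or during the visit | Individualised | Optional | With the letter: possibly before. At check-in or in the visit: may be after | No |
| Printed decision aid at the end of the visit | Individualised | Stated as done, not optional | After | No |

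The possible early release comes from reading two permissions together. The Phase I text says of the values materials that "we may provide this information to patients with the mailed informational letter". It then lets the written recommendations be given at the same moment as a values clarification that precedes the visit. With 2 to 4 weeks between identification and appointment, and randomisation close to the appointment, a posted copy could go out before the arm is known. The text permits this order but does not state it.

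**Step 3: is the gap closed elsewhere?** The opening protocol in the Supplement, since superseded, says under Analysis that control patients will not have received the recommendations by the time of the survey, and that staff will compute the results without sharing them. Amendment 4 has no equivalent sentence. This shows the intended contrast; the change between versions is not itself the fault.

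**Step 4: how large could the effect be?** Suppose a share c of control patients receive the recommendations and respond to them fully. The expected difference is then δ × (1 − c). The documents give no value for c.

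The following is purely illustrative. It borrows the superseded target of 130 surveys and the 15% improvement, and reads the 9 that the protocol labels a standard error as a standard deviation. Two-sided alpha of 0.05 and 65 per arm are assumed.

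- δ = 0.15 × 31 = 4.65 points; standard error of the difference = 9 × √(2/65) = 1.58.
- Power = Φ(δ(1 − c)/1.58 − 1.96).

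| Assumed c | Expected difference | Power |
|---|---|---|
| 0% | 4.65 | 0.84 |
| 20% | 3.72 | 0.65 |
| 30% | 3.26 | 0.54 |
| 50% | 2.33 | 0.31 |

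The table shows only how dilution works. Full response among exposed controls is a pessimistic assumption, and neither the N nor the effect belongs to the current plan.

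**The case against.** The best defence is that the intent is plain. The Phase I steps form one chain: the printed aid goes to the provider, the provider shows it, and the patient takes a copy home. Exception 3 cuts the first link, calls the visit a control visit, and does not require that recommendations be generated. The hypotheses speak of patients who received the recommendations, which implies that others did not. Handing the aid to a control patient would be a strained reading.

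Much of this stands as evidence of intent. It does not close the gap. Staff rather than the provider hand over the take-home copy, recommendations may exist for control visits, and the pre-visit route bypasses the provider altogether.

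Four stronger readings are tempting, and the documents do not support them:

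- **That everything posted precedes randomisation.** No mailing date is given. The described order puts patient contact before chart review and entry of model inputs, so individualised content may not exist when the contact letter goes out. Check-in delivery may follow randomisation, and the take-home copy always does.
- **That the Phase II letter carries intervention material.** The Phase II letter, information sheets and scripts are attached but not shown. They might close part of the gap.
- **That giving the generic sheets to controls is contamination.** The randomised element is the individualised recommendations. Giving generic sheets to both arms would isolate the tailored content and is a legitimate design. What is missing is a statement of which design is meant.
- **That power falls to a particular value.** Amendment 4 requires no set number of surveys and states no effect or power.

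**Conclusion.** The control condition in Amendment 4 is incomplete. It names providers and leaves out patients, while inherited steps can put the individualised recommendations in a control patient's hands before the survey and the one-year record review. The early-release problem concerns the optional pre-visit copy. For the take-home copy, the problem is the missing arm restriction.

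The likely direction is towards no difference. The size cannot be computed, because it depends on the share of controls exposed and on how they respond. A reader might infer that control patients were in fact given the recommendations; the documents do not show that.

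The conclusion assumes that the inheritance clause means what it says and that the attachments not shown do not override exception 3. Pilot status does not remove the point, since Phase II was randomised in order to make this comparison.

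**What to change.** Amend exception 3 to state that:

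1. at control visits the individualised recommendations go to neither provider nor patient by any route (post, check-in, visit or take-home copy) until that patient's Phase II outcomes have been collected;
2. no patient in either arm is given individualised recommendations before the visit has been randomised;
3. the generic shared-decision and values-clarification materials follow one stated rule: either the same in both arms, or intervention arm only and released after randomisation;
4. what each patient received, and when, is logged.

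Check the Phase II letter and scripts against the new wording. For visits already made, state from study records what control patients were given, as far as those records allow. Omit power-loss figures, or label them as illustration.

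The cost is a few sentences, a short log and possibly a revised letter. The drawback is that some intervention patients would get their recommendations at check-in rather than earlier, with less time to read them.

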**Rapid Improvement:** Following each burst, the study team will review feedback and identify next steps. As needed, we will spend approx. 1-4 weeks improving use of the decision aid, the quality of shared decision making (from both patient and provider perspectives), and workflow before implementing the next round. Testing will stop after approx. 4 rounds or when feedback suggests that the process cannot be further improved in an exploratory study. The finished product will represent a tailored decision aid ready for wide-scale testing.

**Cognitive interviews:** Selected patients (particularly early in the study) may be asked to participate in cognitive interviews, to help the study team better understand opinions of the individualized preventive care recommendations. Because these interviews are likely to be short (10-15 minutes), the patients who participate in cognitive interviews will not receive additional compensation.

**Survey mechanics:** The surveys will be administered in RedCAP. Patients will be offered the opportunity to complete the survey immediately after their appointment, on a Cleveland Clinic computer. Alternatively, patients who prefer may complete the survey on their own computer, using the internet. In this case, we will provide patients with the web address and a code required by RedCap. This printout will come directly from RedCap, and an example is enclosed. Finally, if patients prefer, we can ask them the survey questions over the phone. Patients will have 3 business days after their appointment to complete the survey. Survey responses will be confidential, not anonymous, in order to allow researchers to know which patients completed the survey for mailing of gift cards. Answers to the survey questions will not be shared with patient's doctors; participants will be informed of confidentiality.

**Data storage:** Cleveland Clinic Center for Value-Based Care Research investigators will collect data as required by the studies discussed within the protocol. Patient data will be stored on site (in a secure REDCap database) and access will be controlled in accordance to Cleveland Clinic and HIPAA standards. Protected Health Information (PHI) will not be shared outside of Cleveland Clinic.

791

## Amendment 5

792

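### Phase II compares patient outcomes, including one-year service use, only among patients who completed an optional survey after the randomised visit, so the arms compared are not the arms randomised

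*Supplement*

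**What the plan says.** The current text is Amendment 4. Amendment 5 is an interview guide, and the amendment log describes Amendment 6 only as closing enrolment, so neither changes this point.

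- **Randomisation** (Phase II pilot testing, item 3): "Shortly before each appointment at which the decision aid may be discussed, the visit" is allocated to intervention or control. The recommendations go to providers in intervention visits only. Providers are asked to show them to the patient, and a printed copy is handed over at the end of the visit (Phase I text, carried into Phase II).
- **Survey** (item 3 and Survey mechanics): in both arms the patient is asked to take part but will not "be required to complete the survey". "Patients will be offered the opportunity to complete the survey immediately after their appointment", and "Patients will have 3 business days after their appointment to complete the survey".
- **Patient-reported outcomes** (Phase I text, carried over): "For patients who choose to complete the survey, outcomes measures (Appendix C) will include: use of shared decision making", along with preventive care intentions. Item 5 adds the Decisional Comfort Scale.
- **Record review** (item 4): for one year after the visit the team will only "review the medical records of patients who chose to complete the survey". The purpose given is to learn whether the conversations affected the services received. The reason given for the limit is that patients should be aware of the review.
- **Contact before the visit** (Phase I text, carried over): "Study staff will contact eligible patients by mail, telephone or in waiting rooms".

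Amendment 4 names no analysis population, no minimum response, no comparison of responders by arm and no handling of non-response. It describes no blinding.

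**The concern.** Randomisation makes the two full sets of randomised visits comparable. It does not make the survey completers within them comparable. Completion comes after allocation and after a visit at which the aid is shown in one arm only, so the arm may affect who completes. If completion is also related to the outcome, and this differs between arms, a difference between completers can appear without any effect of the aid, or a real effect can be hidden.

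For SDM-Q-9, decisional comfort and intentions, some of this is unavoidable, because only patients who answer can supply the data. For the one-year record review it is avoidable. The outcome sits in the chart whether or not the patient fills in a form, and it addresses the plan's most directly causal question. Making it depend on survey completion discards the benefit of randomisation for that outcome.

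**Working it through.** **1. Order of events.** Pre-visit contact → randomisation → visit (aid shown in the intervention arm only) → survey completed or not, within 3 business days → record reviewed for one year if the survey was completed. The step that defines the analysed set comes after allocation and exposure. It governs both the survey outcomes and the chart outcome.

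**2. The plan's own figures.** Amendment 4 gives no sample size, power or response rate for Phase II, so there is nothing to reproduce. It does keep an SDM-Q-9 mean of 31 and a spread of 9; the text calls the latter a standard error, and I use it as an SD. Two further inputs come from superseded text and serve only for scale:
- completion of one third to one half (Amendment 1), midpoint (0.333 + 0.500)/2 = 0.417;
- a 15% improvement (opening protocol text and Amendment 1), 0.15 × 31 = 4.65 points.

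**3. Illustrative shift in SDM-Q-9 with no true effect.** Suppose a patient completes when a latent normal propensity exceeds a cut-off, and that propensity has correlation ρ with the score. The mean among completers in an arm then shifts by

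SD × ρ × φ(z)/p,

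where p is the completion proportion and z the normal cut-off with upper tail p. Here ρ is the correlation with the latent propensity, not with the yes/no completion variable.

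At p = 0.417, φ(z)/p = 0.9365, and 9 × 0.9365 = 8.43.

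| Assumption | Shift in the difference (intervention minus control) |
|---|---|
| ρ = 0.2 intervention, 0 control | 8.43 × 0.2 = +1.7 |
| ρ = 0.3 intervention, 0 control | 8.43 × 0.3 = +2.5 |
| ρ = 0.5 intervention, 0 control | 8.43 × 0.5 = +4.2 |
| ρ = 0.3 vs 0.15, equal completion | 8.43 × 0.15 = +1.3 |
| ρ = 0.3 in both, completion 50% vs 33% | 9 × 0.3 × (0.798 − 1.097) = −0.8 |
| same ρ and same completion in both | 0 |

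Against the 4.65-point reference, the first three rows are 36%, 54% and 91%.

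**4. A second model.** Let completion be unrelated to the score in control, and let the odds of completion in the intervention arm be multiplied by 1.25, 1.5 or 2.0 per SD of score. The spurious difference is then 1.3, 2.4 or 3.8 points at one-third completion, and 1.0, 1.8 or 2.8 points at one-half. The order of magnitude is the same.

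**5. Record review.** If a share r of each arm is reviewed and nothing is assumed about the rest, each arm's uptake is known only to within 1 − r, so the difference is known to within 2(1 − r). That is 2 × 0.5 = 1.00 at r = 1/2 and 2 × 0.667 = 1.33 at r = 1/3. With equal r in both arms the interval runs from r·d − (1 − r) to r·d + (1 − r), where d is the observed difference. At r ≤ 1/2 it contains zero for every possible d, so without further assumptions the direction of effect is not settled. If records of all agreed and randomised patients were reviewed and complete, this component would be zero for that group.

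**The case against.** **The limit is deliberate.** The plan restricts record review so that patients know of it, and it treats providers as the research subjects. That is a legitimate aim. It does not require the limit, though: a patient letter, scripts and an information sheet already exist and could carry the notice before the visit.

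**The choice may not be made after the visit.** Patients may be contacted by mail, telephone or in the waiting room, and the documents do not say when interest in the survey is first asked. A reader might infer that selection happens entirely after exposure; the text does not establish that. If agreement often comes first, post-visit selection is only the loss between agreeing and completing. What stands is that completion, not prior agreement, decides who is analysed.

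**The survey may be answered much alike in both arms.** It pays $25 in either arm and can be done on site, online or by telephone. That may well keep completion high and similar. Nothing in the plan would show whether it did.

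**The figures rest on assumptions.** This is right. The one-third to one-half completion range comes from a superseded design with two longer surveys (20 and 15 minutes); the current one is a single 10 to 15 minute survey. It is therefore tempting, but unsupported, to say that half to two thirds of Phase II visits will lack outcomes.

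**This is a pilot.** No number of surveys is required, and voluntary surveys after a visit are an ordinary way to measure shared decision making. This lowers the weight of the point. It does not remove it, because Phase II adds randomisation and sets out to examine impact on services.

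**Conclusion.** The point holds for every patient-level outcome in Phase II and most clearly for the one-year record review. Followed as written, the plan compares survey completers by arm rather than randomised patients by arm, for an outcome that needs no survey.

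Three stronger readings should be avoided. Not all Phase II outcomes are affected: provider feedback and interviews do not depend on the patient survey. The documents do not show that results will favour the aid: the illustrations run from −0.8 through zero to +4.2 points, and the sign depends on assumptions that the documents cannot check. Nor is the allocation stated to be unblinded; that follows from showing the aid in one arm only, with no blinding described.

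The numerical range rests on an SD of 9, assumed completion of 42% (or 50% vs 33%) and assumed correlations with a latent propensity. The structural conclusion needs none of these. Severity: should be fixed, given the pilot status.

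**What to change.** **Record review.** Put the record-review notice and a request for agreement into the existing pre-visit letter, script and information sheet, so that agreement is settled before the visit is randomised. Review the records of all agreed and randomised patients whether or not they complete the survey, and analyse that outcome by randomised arm. This meets the awareness aim and removes the dependence on survey completion.

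**Survey outcomes.** Agreement beforehand does not cure non-response to SDM-Q-9, decisional comfort or intentions. For these, report completion by arm with all randomised visits as the denominator. Compare responders with non-responders, within arm, on the chart data extracted for the model among patients who agreed. Label the results as responder-based and add a sensitivity analysis that varies the relation between completion and score by arm, as in the table above. Item 3 makes generating recommendations optional for control visits, so the chart inputs should be extracted in both arms.

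**Visits already randomised.** The log reports enrolment closed, and agreement cannot be added in retrospect. Completion by arm and the sensitivity analysis can still be reported.

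**Cost.** Reworded materials and an IRB amendment. Some patients who would agree only after the visit would not be included, which narrows the population somewhat.
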